##### Usual care

Usual care provided at the SAH is based on MI, with components of CBT [23, 24]. The counselling aims to: develop resistance skills, promote the clients’ motivation to change and prevent recidivism into the use of hazardous amounts of alcohol. Sessions are tailored to the specific needs of each client such as the severity of their alcohol problems and their readiness to change. In practice, the number and duration of counselling sessions vary and the contact mode can be reactive (client-activated) and/or proactive (counsellor-activated). Clients may request contact with the same counsellor in subsequent calls. Since usual care admits multiple counselling sessions, each building on the outcome of the previous one, all client contacts are registered in a computerised client record. Adherence to the agreed contacts is monitored using information from client records. Since usual care is client-activated, there is no standardised protocol for the counselling.

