### Statistical methods

The primary analysis will follow a superiority design applying an intention-to-treat (ITT) approach, i.e., analysing participants based on their random allocation. The alternative hypothesis is that the brief, structured intervention is more effective than usual care in promoting change in a client’s alcohol drinking habits.

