#### Statistical analysis

The primary outcome ‘change in AUDIT risk level’ will be analysed as a dichotomous variable where any downward shift (yes/no) from a higher- to a lower-risk level between baseline and follow-up is considered as a clinically meaningful change in drinking habits. The ratio of the cumulative rates of change in the trial groups will constitute the effect measure of the brief, structured intervention versus usual care. General linear models (GLM) will be used to calculate the RR for the outcome event.

Baseline characteristics will be compared between groups in order to detect potential imbalance in predictors of the outcome. If the two groups are not well balanced according to these predictors, multivariable analysis applying logistic regression models will be carried out to estimate odds ratios for the outcome event.

Secondary outcomes (i.e., depression, anxiety, health measures, care seeking) will be analysed using GLM or logistic regression models as described above.

Complementary ‘per-protocol’ and ‘as-treated’ analyses will also be conducted [30]. The ‘per-protocol’ analysis, will only include participants with complete adherence. Complete adherence is defined as: having used the material and received the proactive call (brief, structured intervention); receiving all counselling sessions agreed between the counsellor and the client (usual care). In the ‘as-treated’ analysis, the number of sessions and total duration of the counselling will be considered for each participant, independent of group allocation. These analyses will contribute to the assessment of the effect of the intervention when delivered in standard practice. Possible confounding effects must be carefully monitored in these analyses, since they ignore the random assignment and, therefore, the distribution of baseline risks between participants.

Moderating factors in the analysis include readiness to change, as well as dose-response, i.e., number and length of calls. Further, process data from the records will provide information on the conduct of the proactive calls (adherence).

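### The per-protocol and as-treated analyses are said to inform the effect in standard practice, but the ITT comparison estimates that effect; the per-protocol contrast compares differently selected adherers

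*Protocol article*

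**What the plan says.** All references are to the protocol article.

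- **Primary analysis (Statistical methods).** It is a superiority comparison "applying an intention-to-treat (ITT) approach, i.e., analysing participants based on their random allocation".
- **Per-protocol set (Statistical analysis).** "The ‘per-protocol’ analysis, will only include participants with complete adherence".
- **Adherence in the brief arm (Statistical analysis).** Two conditions: "having used the material and received the proactive call".
- **Adherence in usual care (Statistical analysis).** One condition: "receiving all counselling sessions agreed between the counsellor and the client".
- **Usual-care dose (Usual care).** In practice "the number and duration of counselling sessions vary". Sessions are tailored to severity and readiness to change, and there is no standard counselling protocol.
- **As-treated analysis (Statistical analysis).** Number of sessions and total duration are considered for each participant, whatever the allocated arm.
- **Interpretation (Statistical analysis).** "These analyses will contribute to the assessment of the effect of the intervention when delivered in standard practice". The sentence covers the per-protocol and as-treated analyses together. The next sentence says that confounding needs careful monitoring because these analyses disregard the random assignment. It names no method of adjustment.

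**The concern.** Two things do not fit together. First, the effect of a counselling model in ordinary use includes clients who do not open the booklet, miss the call or drop agreed sessions. A set confined to complete adherers removes those clients, so it addresses a different question, namely the effect under full adherence. The as-treated analysis relates outcome to the amount of counselling received and is not a randomised comparison of the two models either.

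Second, the two adherent sets are formed by different rules. The brief-arm target is fixed. The usual-care target is negotiated with each client after randomisation, in sessions tailored to severity and readiness to change, both plausible predictors of outcome. A usual-care client who agreed to little meets the rule easily, while one who agreed to many sessions and missed one is excluded. The brief-arm rule does not mention clients who call back and receive usual counselling.

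At stake is how a per-protocol or as-treated difference would be read. The Discussion says that results will first be used locally to develop the helpline. A selection artefact presented as bearing on standard practice could colour that reading.

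**Working it through.** **The plan's own figures.** The plan gives no figure for the per-protocol analysis, so there is none to reproduce. The only planning value used here is the 30% usual-care rate of downward AUDIT shift (Sample size). For context, the ITT power statement of more than 90% for 30% versus 50% with 125 per arm reproduces:

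- Null SE = √(2 × 0.40 × 0.60 / 125) = 0.0620
- Alternative SE = √((0.30 × 0.70 + 0.50 × 0.50) / 125) = 0.0607
- z = (0.20 − 1.96 × 0.0620) / 0.0607 = 1.29, so power is 0.902 (two-sided 5%, normal approximation)

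This point does not affect it.

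**Side by side.**

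| Question | ITT | Per-protocol |
|---|---|---|
| Who is compared | Everyone, as allocated | Complete adherers only |
| Non-adherence | Included | Removed |
| Selection after randomisation | Not by adherence | Yes, by a different rule in each arm |
| Question answered | Effect of offering each model as used | Effect under full adherence, if selection is handled |

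The quoted interpretation sentence attaches the left-hand question to the right-hand analysis.

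**Can selection alone move the RR?** Assumptions, none of them from the document: no true arm effect; half the clients are motivated, with a 40% shift rate, and half are not, with 20%. The overall rate is 0.5 × 0.40 + 0.5 × 0.20 = 30%, as in Sample size. If a proportion a of motivated and b of unmotivated clients adhere, the rate among adherers is

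(0.40a + 0.20b) / (a + b).

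| Brief arm a/b | Usual care a/b | Rate, brief | Rate, usual care | Per-protocol RR |
|---|---|---|---|---|
| 80%/60% | 80%/60% | 31.4% | 31.4% | 1.00 |
| 80%/40% | 70%/70% | 33.3% | 30.0% | 1.11 |
| 80%/40% | 60%/80% | 33.3% | 28.6% | 1.17 |
| 80%/60% | 80%/40% | 31.4% | 33.3% | 0.94 |
| 90%/90% | 80%/40% | 30.0% | 33.3% | 0.90 |

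Row 2, for example: (0.32 + 0.08) / 1.20 = 33.3%, (0.28 + 0.14) / 1.40 = 30.0%, ratio 1.11. The ITT RR is 1.00 in every row.

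**Stronger assumptions.** Take a continuous engagement trait with an odds ratio for success of 1.5 to 2.5 per SD, correlated 0.5 or 0.8 with adherence, with 70% adherent in the brief arm and 30% to 50% in usual care. The null per-protocol RR is then 0.78 to 0.96. If the correlation is reversed in usual care only (clients who do well stop attending), it is 1.20 to 2.34. With 70% adherent in both arms and the same correlation, it is 1.00. The shift therefore needs selection that differs between arms.

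**The case against.** The case on the other side is substantial, and most of it stands.

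- **The plan is more cautious than a quick reading suggests.** A reader might infer that it takes the per-protocol result as the effect in standard practice. The text does not say that. It says these analyses contribute to the assessment, calls them complementary and keeps ITT primary.
- **The bias is not overlooked.** The plan states that these analyses set randomisation aside and that confounding is possible. Adjustment details may also sit in an analysis plan that is not shown, so their absence is not counted here as a fault.
- **Arm-specific rules are partly unavoidable.** A booklet with one call and a client-driven service cannot share one adherence definition. A reader might also shorten the brief-arm rule to receipt of one call, but it requires use of the material as well.
- **Zero agreed sessions is an inference.** Procedure of recruitment says that a proactive call is scheduled for usual-care participants only if they agree. A reader might conclude that clients with no agreed session count as fully adherent. The document does not say so, and usual care also includes calls that the client makes.
- **The numbers are illustrations.** Adherence rates and correlations are assumed, and the extreme values need several strong assumptions at once.
- **The decision rule.** The Discussion ties a change of service to proven superiority, and superiority is tested by ITT. Nothing says that the helpline would act on a per-protocol result.

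None of this rescues the interpretation sentence. Contributing evidence on standard practice is still the wrong role for an analysis that removes incomplete adherers, and monitoring confounding does not correct it.

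**Conclusion.** The point holds as a minor one about interpretation and about what the per-protocol contrast can support. The effect in standard practice, with ordinary non-adherence, is what the primary ITT analysis estimates. The per-protocol contrast compares two subsets selected differently after randomisation, and its RR can lie on either side of 1 when there is no true effect.

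The size cannot be determined, because the document gives no adherence rates and no relation between adherence and outcome. The range of 0.90 to 1.17 shows direction and rough scale under mild assumed patterns. The wider ranges need strong assumptions and are not predictions. A reader might infer from them that the trial's conclusion is in danger. The document does not support that, since the primary comparison does not depend on adherence.

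**What to change.** 1. **Reword the interpretation sentence in Statistical analysis.** State that the ITT analysis estimates the effect in standard practice. State that the per-protocol and as-treated results are exploratory, non-randomised estimates, that the per-protocol one addresses the effect under complete adherence, and that neither supports a claim about standard practice.
2. **Adjust or weight the per-protocol analysis where it is reported.** Model adherence within each arm on baseline predictors: AUDIT score, sex, age, M.I.N.I., self-rated health, sick leave and earlier help-seeking. Add readiness to change if it is measured at baseline; the plan names it as a moderator, but the Data collection section does not list it in the questionnaire. With inverse-probability-of-adherence weights, use robust standard errors, so that both adherent sets are standardised to the randomised population.
3. **Show usual-care clients with no agreed session separately, if there are any.**

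The cost is a few sentences of wording and modest analysis work, mostly on data already planned for collection. The downside is that only measured predictors of adherence are handled, so unmeasured engagement can still bias the result, and the interval widens somewhat. The results therefore stay exploratory after weighting. The primary analysis and the sample size do not change.

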#### Trial arms

##### Brief, structured intervention

This intervention includes the delivery to participants of a self-help booklet followed by one proactive call from a counsellor at the SAH. The self-help booklet is designed as a guide to change alcohol use patterns using a cognitive behaviour therapy (CBT) framework. The booklet is developed by the Clinic for Alcohol and Health in Stockholm City, slightly modified for the SAH setting. The structure follows a step-by-step approach; starting from the clients’ initial reflections and motivation to change, proceeding to goal-setting and self-monitoring of their drinking behaviour. In addition, the material contains suggestions on how to practically accomplish behaviour avoidance and resistance skills. The booklet is provided by e-mail, mail or through a password-protected website. After 2 weeks from the dispatching of the booklet, the client is contacted by a proactive call from a counsellor at the SAH which has the scope to assess and guide the use of the material as well as to discuss the client’s progress. After the proactive call, no further contact with the client is initiated by counsellors at the SAH. However, clients are not discouraged from calling the SAH again if they feel the need to do so. If a further contact is initiated by the client, usual counselling is provided. The intervention is delivered according to a protocol and all contacts are logged in a computerised client record which is also used to monitor intervention adherence.

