### Randomisation

A computer-generated sequence of serial numbers for up to 1000 participants paired with a random series of allocation numbers (1 for usual care or 2 for the brief, structured intervention) is used to allocate the participants to either trial group. The allocation sequence is based on simple randomisation and is concealed to counsellors, clients and interviewers until the baseline interview is performed. The research coordinator prepares the sequential numbered, sealed envelopes containing a folded note of the group allocation. At the end of the baseline interview, interviewers open the sealed envelope according to the serial number sequence and disclose the allocation, i.e., assign clients to the trial condition.

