### Data collection

The assessment of clients’ characteristics and of the outcome is conducted using a structured questionnaire with closed-ended response alternatives administered via telephone interviews at baseline, 6-month and 12-month follow-up. The questionnaire includes demographics, the AUDIT scale, self-rated health, sick leave, depression or anxiety symptoms (M.I.N.I.) and help-seeking due to problematic alcohol use. Figure 2 displays the process of recruitment, allocation according to the SPIRIT guidelines.

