**Fig. 2 Fig2:**
[figure not shown]
Standard Protocol Items: Recommendations for Interventional Trials (SPIRIT) schedule of enrolment, intervention and assessment, including information of staff members and task duration. *Usual care – tailored counselling mixed approach reactive and proactive calls as agreed. Starts from week 1 or when client wishes to contact the Swedish National Alcohol Helpline (SAH) and continues as needed

The baseline interview is conducted 5–15 working days after the first call. Follow-up interviews are collected 26 weeks (±2) and 52 weeks (±2) after the baseline interview.

A maximum of five call attempts are made to reach participants at each stage of the data collection, and text messages are additionally used as alerts or to schedule interviews. A research coordinator ensures that participants are followed-up within the appropriate time interval. Data of the process, compliance to the study protocol and adherence of the client will be gathered from the client records kept at the SAH. Available information includes: conduct of proactive and reactive calls as agreed, number of contacts during the study period, and length of each contact.

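### Number and length of calls are listed as moderators, but they arise after randomisation and depend on arm and client, so the moderator analysis can mislead

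*Protocol article*

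**What the plan says.** The protocol article's Statistical analysis section ends with a short paragraph on moderators: "Moderating factors in the analysis include readiness to change, as well as dose-response, i.e., number and length of calls". A client characteristic and two measures of counselling received are thus given the same role.

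The paragraph before it describes the per-protocol and as-treated analyses. The as-treated analysis already uses session number and total duration, whatever the allocated arm. It comes with a warning that confounding needs watching because these analyses set the random assignment aside. The moderator paragraph has no such warning.

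Other sections fix the timing and the sources of the call data:

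- Randomisation: "At the end of the baseline interview, interviewers open the sealed envelope according to the serial number sequence and disclose the allocation".
- Data collection (text after Fig. 2), on what the client records supply: "conduct of proactive and reactive calls as agreed, number of contacts during the study period, and length of each contact".
- Brief, structured intervention: "After the proactive call, no further contact with the client is initiated by counsellors at the SAH", but also "If a further contact is initiated by the client, usual counselling is provided".
- Usual care: "In practice, the number and duration of counselling sessions vary and the contact mode can be reactive (client-activated) and/or proactive (counsellor-activated", and "Sessions are tailored to the specific needs of each client such as the severity of their alcohol problems and their readiness to change".

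**The concern.** A moderator analysis asks whether the effect of allocation differs between kinds of client. Randomisation supports the answer only if the variable that defines the kinds could not have been changed by allocation. Within levels of such a variable the arms remain comparable.

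Number and length of calls fail this condition. Contact intensity is a large part of what differs between the arms, and within each arm it also depends on the client. Clients with the same number of calls in the two arms may therefore be different sorts of client, and a comparison at a fixed call count is no longer a randomised one.

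The trial is meant to inform how the helpline develops its service. A finding that the effect depends on how many calls a client has could be taken as evidence on how much contact to offer. As specified, it would not be evidence of that.

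**Working it through.** The plan states no figure on this point. The check sets the passages in order and then tests the mechanism by simulation.

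**Order of events**

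1. Allocation is disclosed at the end of the baseline interview (Randomisation).
2. The call variables count and time contacts during the study period (Data collection). They therefore follow allocation.
3. Arm affects them. The brief arm has one planned proactive call and no later counsellor-initiated contact; usual care has a variable number of calls that either side may start.
4. Client traits affect them. Usual-care sessions are adapted to severity and readiness to change; further calls in the brief arm are made by clients who feel the need. Severity and readiness are plausible predictors of a fall in AUDIT risk level.
5. Points 3 and 4 together mean that conditioning on calls conditions on a joint consequence of arm and prognosis.

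**Simulation**

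Taken from the document: 125 analysed per arm, and a 30% rate of downward shift (Sample size). Everything else is assumed:

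- Outcome: logit P(shift) = ln(0.30/0.70) + 0.8U, where U is a standard normal client trait. There is no effect of arm and none of calls.
- Calls: 1 + Poisson(m), with m = 2.0·exp(b_UC·U) in usual care and m = 0.4·exp(b_BI·U) in the brief arm, capped at 15.
- At U = 0 the share with two or more extra calls is 1 − e^(−0.4)(1 + 0.4) = 6.2% in the brief arm and 1 − e^(−2)(1 + 2) = 59.4% in usual care, so the arms overlap in part.
- Analysis: logistic regression on arm, calls and arm × calls; 1,500 replicates per row; tests at 5%.

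| How the trait drives calls | b_UC | b_BI | Interaction rejected | Arm coefficient rejected |
|---|---|---|---|---|
| Not at all | 0 | 0 | 5.1% | 5.1% |
| Equally in both arms | 0.4 | 0.4 | 5.4% | 8.1% |
| In usual care only | 0.5 | 0 | 9.0% | 22.6% |
| Opposite directions | 0.5 | −0.5 | 42.9% | 56.5% |
| Opposite directions | 0.4 | −0.8 | 65.2% | 64.1% |
| Opposite directions | −0.5 | 0.5 | 48.4% | 53.0% |

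The Monte Carlo standard error near 5% is √(0.05 × 0.95/1500) = 0.6 percentage points. The first two interaction figures are therefore at the nominal level and 9.0% is above it.

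Calls were not centred, so the arm coefficient is the contrast extrapolated to zero calls. Its true value is zero at every call count, so rejections above 5% still reflect bias.

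False modification thus appears when traits drive calls differently in the two arms. The arm coefficient is distorted sooner, already to some extent when the drive is equal.

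**The case against.** The strongest reply is that the fault is mainly one of labelling. The sentence speaks of dose-response and directly follows the as-treated paragraph, which uses the same variables and does warn of confounding. No arm × calls interaction and no stratification by calls is written down. Read this way, the authors intend a dose analysis and have only used the wrong word. The reading is possible, but it does not clear the sentence. The text calls these variables moderating factors alongside readiness to change, and a dose analysis would be confounded too, with no warning attached to it here.

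The reply is right to limit the point, and four stronger readings should be resisted:

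- A reader might infer that false effect modification is bound to appear. The simulation contradicts this: the interaction test stayed near 5% in two of the six settings.
- A reader might infer that calls are fixed by arm, so that hardly any brief-arm client has many calls. Only counsellor-initiated contact is limited in that arm. Clients may call again and then receive usual counselling, and the article gives no distribution of calls.
- A reader might infer from the list of questionnaire contents, "The questionnaire includes demographics, the AUDIT scale, self-rated health, sick leave, depression or anxiety symptoms (M.I.N.I.) and help-seeking due to problematic alcohol use", that readiness to change is not measured. The list need not be exhaustive, and a condensed article may leave such detail to the full protocol.
- A reader might infer that the main result is at risk. The primary analysis compares participants as randomised and does not use call data.

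**Conclusion.** Wrong as written, in a supplementary analysis. Number and length of calls follow randomisation and are affected by the assigned arm and by client severity, readiness and need. Used as moderators, they can yield a distorted arm effect or false effect modification, and the plan's warning does not reach them.

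That these variables follow allocation and depend on arm and client rests on the document alone. The size of any bias does not. It depends on how strongly, and how differently, client traits drive calls in the two arms, which the article does not report. On the assumed settings, false-positive rates ran from the nominal 5% to about 65%; these show the mechanism and do not forecast this trial. What changes is how a dose-related result may be interpreted. The primary comparison stands.

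**What to change.** Four changes to the Statistical analysis section:

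1. Limit moderator analyses to variables measured before randomisation, such as readiness to change at baseline.
2. Remove number and length of calls from the moderators.
3. Analyse them only as post-randomisation exposure, within the as-treated/dose-response analysis already planned, adjusted for baseline prognostic variables.
4. Extend the existing confounding warning to that analysis and label it exploratory and non-causal.

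Possible wording: *Effect modification will be examined only for variables measured before randomisation, such as baseline readiness to change. Number and length of calls are post-randomisation measures of exposure. They will be analysed in the as-treated/dose-response analysis, adjusted for baseline prognostic variables, and reported as exploratory, without causal interpretation.*

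The cost is a change of wording before the analysis. The call data are already collected, and the sample size, the primary analysis and the conduct of the trial stay as they are.
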